### Interventions

*Coping with COVID* (CWC). The CWC programme is a brief psychological intervention developed to reduce symptoms of stress (e.g., depression, anxiety) for those affected by ongoing adversity. This programme was adapted to include evidence-based strategies that specifically target COVID-19 related distress in a young adult population. This includes education about common reactions to COVID-19, stress management (i.e., slow diaphragmatic breathing), problem solving, worry management, behavioural activation, skills to strengthen access to social support, and relapse prevention. CWC will be delivered over 6 weekly sessions of 60-minute duration. The programme will be delivered in anticipated group size of 4–5 participants via the Google Meet online platform.

*Supportive Counselling (SC).* The SC arm will involve 6 weekly 60-minute video-conferencing sessions that will be led by a trained peer facilitator, who will facilitate group discussions about how students are coping with the pandemic, ventilation of reactions to problems experienced, and discussion of possible solutions. Those randomised to the SC arm will not receive support relating to CWC strategies.

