### Sample size

The sample size calculation for this treatment trial was based on a two-group comparison of the primary outcome at the 2-month follow-up timepoint. In order to obtain estimates of parameters, a comparable data set from a recent treatment trial in a high-income setting was used [20]. The power analysis indicated that to achieve a moderate effect size of (0.6) a sample size of 90 participants would be needed per arm to provide power of 0.95 (alpha = 0.05, two-sided); on the expectation that there would be approximately 10% attrition at the 2-month follow-up assessment, it was estimated that a total of 200 participants would need to be enrolled into the study.

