### Statistical analysis

Baseline comparability between CWC and SC conditions will be analysed using multiple planned comparisons for continuous measures, and chi-squared tests for categorical variables. Hypothesis testing involving assessment of differential change over time between groups will be assessed using Hierarchical Linear Mixed Modelling (HLM). This HLM statistical method presumes an intent-to-treat framework by allowing the number of observations to vary between participants and thereby effectively handles missing data. For each outcome, linear effects of time of measurement, condition, and condition-by-time interaction will be analysed. Fixed effects parameters for the time of assessment and intervention condition will be tested with the Wald test (t-test, *p* < 0.05, two-sided) and 95% confidence intervals. Cohen’s (d) effect size will be calculated for all analyses. Analyses will focus on the primary outcome (HADS) and secondary outcomes (GAD-7, CSS, SIDAS, & WHO-5) for both CWC and SC, with the main outcome time point being the 2-month follow-up, relative to baseline. To assess for potential bias from attrition, completer analyses will also be conducted using only the data on participants completing the allocated intervention as planned. Two-tailed tests will be reported with a significance level of *p* < 0.05 for all analyses.

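### The completer analysis planned as the check on attrition bias selects on finishing the sessions, not on having follow-up data, so it cannot serve that purpose

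*Protocol article*

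**What the plan says.** The Statistical analysis section of the protocol article specifies a hierarchical linear mixed model on all available observations. It describes the model as "allowing the number of observations to vary between participants and thereby effectively handles missing data", without naming the assumption under which that is true. It then adds a second analysis with a stated purpose: "To assess for potential bias from attrition, completer analyses will also be conducted using only the data on participants completing the allocated intervention".

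The Sample size section allows for "approximately 10% attrition at the 2-month follow-up assessment" and concludes that "it was estimated that a total of 200 participants would need to be enrolled into the study". There, attrition means that the T2 assessment is not obtained.

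What it means to complete the intervention comes from the Interventions section: "CWC will be delivered over 6 weekly sessions of 60-minute duration". Supportive Counselling (SC) has the same number and length of sessions. Outcomes are collected by online survey, separately from the sessions (Data management and trial monitoring).

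**The concern.** Attrition bias arises when T2 scores are missing for reasons related to their unseen values. The planned check selects on a different event, finishing the sessions. Because outcomes are collected by survey, one participant may stop sessions and still return T2, and another may finish the sessions and not return it. The check discards the first participant's observed score. It leaves the second participant's score missing on the same terms as in the main model.

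The completer set is also defined by something that happens after randomisation. If the reasons for stopping relate to outcome differently in a taught skills programme and in open group discussion, completers in the two arms are no longer comparable.

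What is at stake is interpretation. A completer result that matches the main result could be reported as evidence that attrition did no harm, and one that differs could be blamed on attrition. Neither reading would be justified.

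**Working it through.** **1. What attrition means in the plan.** Inputs from Sample size: 90 per arm and 10% attrition at the 2-month assessment. 2 × 90 / (1 − 0.10) = 200, which reproduces the stated enrolment. The inflation is there to keep 90 per arm with T2 data, so attrition is counted as missing T2 assessments. (The 90 itself does not follow from an effect of 0.6 at 95% power: 2 × (1.960 + 1.645)² / 0.6² ≈ 72.2, or 73 per arm. Nothing below depends on this.)

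**2. The two events side by side.**

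| Participant | Main mixed model | Completer analysis |
|---|---|---|
| Finished sessions, T2 observed | Used | Used |
| Stopped sessions, T2 observed | Used | Dropped, although nothing is missing |
| Finished sessions, T2 missing | Missing at random assumed | Kept, under the same assumption |
| Stopped sessions, T2 missing | Missing at random assumed | Dropped |

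The check removes the second and fourth rows and leaves the third as it was. In no row does it vary the assumption about a missing T2 score.

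**3. Can the check differ when there is no attrition?** Assumed: outcome SD 1, true difference 0, every T2 score observed, correlation 0.6 between time points. Completion in Coping with COVID (CWC) has probability expit(1.7 − 0.8 × T2 score), about 82%. Completion in SC is 80% at random. Large-sample simulation gives these completer contrasts (CWC minus SC; negative favours CWC):

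| Mechanism in CWC | Raw T2 means | Change from baseline | Baseline-adjusted |
|---|---|---|---|
| Stopping depends on T2 score | −0.13 | −0.05 | −0.09 |
| Stopping depends on post-treatment score | −0.08 | 0.00 | −0.03 |
| T2 mechanism in both arms alike | 0.00 | 0.00 | 0.00 |

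The change-from-baseline figure follows from the raw one. Selection that shifts T2 by −0.133 shifts baseline by 0.6 × −0.133 = −0.080, and the difference is −0.053. With every T2 score observed, the all-participant estimate is 0.00 throughout.

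**4. Can the check agree when attrition bias is present?** Assumed: everyone finishes the sessions, T2 is missing in CWC with probability expit(−2.6 + 1.2 × T2 score), about 11%, and in SC at random for 10%; the true difference is 0. An estimate that assumes missing at random, using baseline and post-treatment scores, is −0.07 SD. The completer estimate is also −0.07 SD, because the completer set is the whole sample. The bias is present and the check shows no discrepancy.

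**5. Size of the underlying problem at the planned attrition.** If 10% of one arm is missing and the unseen scores differ by 0.5 SD from what missing at random implies, the contrast moves by 0.10 × 0.5 = 0.05 SD, or 0.05 / 0.6 ≈ 8% of the target effect.

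**The case against.** The strongest case against is that the completer analysis is additional, the primary analysis uses all available observations under intent-to-treat, and nothing says that the completer result would override it. This stands, and it limits the harm to the supplementary analysis.

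A reader might infer that the trial has no other check on missing data. The documents do not support that. This is a condensed article, and a full protocol or SAP may contain sensitivity analyses. The point rests on a stated analysis that is given a purpose it does not serve, not on what the article leaves out.

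A reader might also infer a bias of 0.13 SD, over a fifth of the target. That figure belongs to raw T2 means, whereas the plan analyses change over time relative to baseline. It also requires outcome-related stopping in one arm only. Both arms have six weekly 60-minute peer-led video sessions, so strongly arm-specific stopping is an assumption. With the same mechanism in both arms the bias is zero. For scale, the standard error of a T2 contrast with 90 per arm is about √(2/90) = 0.15 SD.

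Nor do the documents show how many people will stop sessions and still return T2. If nearly all who stop are also lost to follow-up, the completer set approximates the observed set, and a marked disagreement would be a crude warning. It would therefore be too strong to call the check wholly uninformative. What remains is that agreement cannot rule out bias from scores missing not at random, and disagreement has more than one explanation.

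**Conclusion.** The concern holds in a limited form. The Statistical analysis section assigns the assessment of attrition bias to a subset defined by adherence, while the Sample size section counts attrition as loss at T2. The method does not serve its stated purpose, and that would remain so whatever an SAP adds. The statement that the model "thereby effectively handles missing data" is true only under missing at random given the modelled data, and the completer analysis does not probe that assumption.

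The size is modest. Under the assumed T2-driven one-arm mechanism, with about 80% completion and a correlation of 0.6, the spurious completer difference is about 0.05 to 0.09 SD for baseline-referenced estimators. It is smaller or zero under the milder mechanisms shown. The documents give no completion rate or correlation, so these values are illustrations, not predictions.

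The primary mixed model is not made wrong by any of this. The likely consequence is false reassurance or false alarm, not reversal of an effect of 0.6. It should be corrected, but it does not threaten the trial.

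**What to change.** - Relabel the completer analysis as a supplementary per-protocol (adherence) description and remove its stated role as the check on attrition bias.
- State that the mixed model handles missing outcomes under missing at random given the observed scores in the model.
- Make the attrition-bias check a sensitivity analysis of T2 HADS in all randomised participants. Delta-adjusted multiple imputation is one suitable choice, with delta varied separately by arm, for instance until the conclusion changes. Any method that relaxes missing at random in the full randomised set would do.
- Report the number and percentage with missing T2 HADS by arm.

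If an SAP already contains such an analysis, only the first two changes are needed, with a cross-reference. The cost is a wording change and a few hours of analysis, with no new data.

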## Discussion

This study will evaluate CWC in managing COVID-19 related distress in the sequalae of the COVID-19 pandemic. The trial outlined in this protocol is the first to assess the effectiveness of the CWC program relative to an active control intervention, and in a LMIC setting with young adults in a college-going population. The extent to which the effectiveness of CWC relative to SC is demonstrated, this trial will shed important insights on the active components of this transdiagnostic intervention.

## Data Availability

Not applicable.

## Abbreviations

CWC: Coping with COVID
CSS: COVID Stress Scales
GAD-7: Generalized Anxiety Disorder Scale
HADS: Hospital Anxiety and Depression Scales
HADS-A: Hospital Anxiety and Depression Scales -Anxiety Subscale
HADS-D: Hospital Anxiety and Depression Scales -Depression Subscale
HIPPAA: Health Insurance Portability and Accountability Act
HLM: Hierarchical linear modeling
K10: Kessler- 10 item version
LMIC: Low- and Middle-Income Countries
PHQ-9: Patient Health Questionnaire – 9 item version
PM+: Problem Management Plus
RCT: Randomized Controlled Trial
SC: Supportive Counselling
SIDAS: Suicidal Ideation Attributes Scale
WHO: World Health Organization
WHO-5: World Health Organization Wellbeing Index
